**Methods:** This study is a multicenter, randomized, double-blind, placebo-controlled clinical trial. A total of 388 eligible subjects were recruited from the First Hospital of Hunan University of Chinese Medicine, Hunan Academy of Chinese Medicine Affiliated Hospital, the First Hospital of Shaoyang University, the First Traditional Chinese Medicine Hospital of Changde, and Jiangmen Wuyi Hospital of Traditional Chinese Medicine from July 2020 to April 2022. After a 4-week run-in period, all participants were divided into the intervention group (represented by Y-T, N-T) and control group (represented by Y-C, N-C); using a stratified block randomized method based on the presence or absence of brain damage symptoms in hypertensive cerebral small vessel disease (represented by Y and N). The Y-T and N-T groups were administered different doses of naotaifang capsules, whereas Y-C and N-C groups received placebo treatment. These four groups received the treatments for 6 months. The primary outcome included Fazekas scores and dilated Virchow-robin spaces (dVRS) grades on magnetic resonance imaging (MRI). The secondary outcomes included the number of lacunar infarctions (LI) and cerebral microbleeds (CMB) on magnetic resonance imaging, clinical blood pressure (BP) level, traditional Chinese medicine (TCM) syndrome scores, mini-mental state examination (MMSE) scale, and safety outcomes. Fazekas scores, dilated Virchow-robin spaces grades, and the number of lacunar infarctions and cerebral microbleeds on magnetic resonance imaging were tested before enrollment and after 6 months of treatment. The clinical blood pressure level, traditional Chinese medicine syndrome scores, mini-mental state examination scale and safety outcomes were tested before enrollment, after 3-month, 6-month treatment and 12th-month follow-up respectively.

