**Conclusion:** The protocol will comfirm whether naotaifang capsules reduce Fazekas scores, dilated Virchow-robin spaces grades, and the number of lacunar infarctions and cerebral microbleeds, clinical blood pressure, increase mini-mental state examination scores, traditional Chinese medicine syndrome scores of Qi deficiency and blood stasis (QDBS), and improve the quality of life of subjects. The consolidated evidence from this study will shed light on the benefits of Chinese herbs for hypertensive cerebral small vessel disease, such as nourishing qi, promoting blood circulation and removing blood stasis, and dredging collaterals. However, additional clinical trials with large samples and long intervention periods will be required for in-depth research.

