### Types of outcomes

#### Primary outcome

The Fazekas scores and dVRS grades will be obtained for both groups. The specific scoring criteria are described in the diagnostic criteria. Brain MRI examinations will be performed before enrollment and after 6 months of treatment.

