### Sample size calculation

At present, there is no clinical research report on TCM treatment for WML of CSVD. According to our previous case-control study, Fazekas grades of WML are an independent risk predictor of stroke (*p* < 0.01). With WML levels of 0–3 increasing step by step, delayed memory, spatial, and executive dysfunction appear at WML level 2, specifically at WML level 3. The mean ± standard deviation (SD) of Fazekas scores of HT-CSVD patients was 2.29 ± 1.26 (Zhou et al., 2022). After 6 months of NTF treatment, the mean ± SD of Fazekas scores is 2.29 ± 1.26 for the intervention group and 2.8 ± 1.3 for the control group (since CSVD is a progressive brain disease, we speculate that Fazekas grades of control groups will increase at least 0.5 points after 6 months without intervention). Considering α 10% significance level, the Z-value is based on the Z-value table for two-tailed distribution of 1.65. The β-value is determined at 0.20, and the Z-value is based on the Z-value table for a one-tailed distribution of 0.85. When the dropout rate is 20%, the sample size is calculated using an estimation formula for comparison of the mean values of two independent samples as follow:
$$N=\frac{{\left(Z_{\alpha /2}+Z_{\beta }\right)}^{2}*{\left(1+1/k\right)\;\sigma }^{2}}{\delta^{2}}=\frac{{\left(1.65+0.85\right)}^{2}*2*\left({1.26^{2}+1.3}^{2}\right)/2}{0.5^{2}}=81$$

Where N is the sample size of each group; Z_a_ is the table of Z-value for two-tailed distribution; Z_β_ is the table of Z-value for one-tailed distribution; σ is the standard deviation; δ represents the difference. The number of cases that may drop out is added; thus, 388 subjects will be required.

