### Statistical analysis

All statistical analyses will be performed using the SPSS 22.0 statistical software. Descriptive statistics will be used for baseline characteristics data. Quantitative variables (numerical variables) will be analyzed by the normality test (such as *Shapiro-Wilk*), and normal distribution numerical variables will be compared using two independent *t*-tests or analysis of variance (*ANOVA*) and other potential confounding variables (such as multicenter characteristics) as covariates. Numerical variables will be summarized with mean ± SD. Non-parametric tests (*Wilcoxon rank-sum* test, *Kruskal–Wallis* test) and M (P_25_, P_75_) will be used to describe the non-normal distribution. Qualitative variables (categorical variables) are represented by the number of cases and the composition ratio; comparison among groups will be performed using the chi-square test or Fish precision probability. Non-parametric test or analysis of covariance will be used to compare the difference in therapeutic indexes. The efficacy analysis adopts the intention to treat (ITT) analysis and the per-protocol set (PPS). Subgroup analysis will be performed regardless of whether the treatment significant effect the main outcome. Safety analysis will be performed by analyzing the incidence of intergroup AEs and abnormal laboratory examination results before and after treatment.

The full analysis set (FAS) will be conducted for the therapeutic indexes of all subjects included in the study. Statistical analysis in accordance with PPS will be conducted for the therapeutic indexes of subjects completing the drug intervention for 6 months. FAS uses the last-observed-carried-forward method (LOCF) to adjust the missing data and complete ITT analysis. The safety analysis will be performed using the safety analysis set (SS). All statistical tests will be two-sided. *p* ≤ 0.1 means there is a statistical difference, *p* ≤ 0.05 represents a significant statistical difference.

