Based on TCM theories and clinical evidence, our research team developed NTF as a new Chinese medicine formula for treating cerebral vascular diseases. We performed a series of investigations to evaluate the pharmacology, efficacy, and safety of NTF for more than 20 years. Studies indicate that NTF and its extracts minimize the cerebral infarct size and improve neurological function by inhibiting inflammation, oxidative stress, and apoptosis (Liao et al., 2015; Lan et al., 2020; Yang et al., 2021; Zhao et al., 2021). Considering the shared pathogenesis pathways between HT-CSVD and ischemic stroke, and if HT-CSVD is not treated in time, it can gradually progress to stroke. Therefore, we speculate that NTF capsules may also be effective against HT-CSVD. Recruitment of participants commenced in July 2020, and the trial is expected to be completed in December 2022. The findings from this study will reassess the effecacy and safety of NTF capsules through a multi-center, double-blind RCT. Moreover, the results of this study will guide the clinical treatment of HT-CSVD and the prevention of other conditions, including stroke and other cerebral macrovascular diseases.

Noteworthy, this trial is still an exploratory study, hence the sample size and clinical research sub-centers may be insufficient. Also, improving participant compliance with medication is a critical issue and worthy of attention, considering that they are elderly with basic diseases. Of importance is that the intervention period of this study is relatively short, and the long-term efficacy and safety will be determined in follow-up studies. Therefore, additional multicenter-clinical trials with large sample sizes and long intervention periods are essential for comprehensive research.

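### Two unranked primary outcomes and two p-value tiers leave the deciding rule open; if either outcome may succeed at p ≤ 0.1, the false positive rate is about 19% against a 10% design level.

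*Protocol article*

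**What the plan says.** - **Outcomes.** The Abstract (Methods), Table 1 and the Primary outcome section all name Fazekas scores and dVRS grades together. The Primary outcome section says: "The Fazekas scores and dVRS grades will be obtained for both groups". None of these places ranks the two or says whether one or both must succeed.
- **Sizing.** The Sample size calculation uses Fazekas means and SDs only: "Considering α 10% significance level, the Z-value is based on the Z-value table for two-tailed distribution of 1.65". No assumption is given for dVRS.
- **Decision levels.** The Statistical analysis section makes every test two-sided. It then sets two tiers: p "≤ 0.1 means there is a statistical difference", and p "≤ 0.05 represents a significant statistical difference". It does not attach either tier to the primary conclusion.
- **Status.** Table 1 lists Phase II. The Discussion says "this trial is still an exploratory study", while the Abstract (Conclusion) says "The protocol will comfirm whether naotaifang capsules reduce Fazekas scores" and continues through a list of further outcomes.

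**The concern.** The article fixes two labels for a positive result and two primary outcomes that can earn them, but not how these combine into one conclusion. A p of 0.08 on dVRS alone, with nothing on Fazekas, already meets the article's definition of a difference on a primary outcome. The reader could not tell whether the trial had succeeded, or what error rate stood behind that statement. The 10% level in the sample size section applies to one test of one outcome. It is not the error rate of a conclusion that either outcome may carry.

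**Working it through.** **Inputs.** Sample size calculation: SDs 1.26 and 1.3, difference 0.5, Z values 1.65 and 0.85, dropout 20%, total 388. Randomization: 194 codes per stratum at 1:1, so 97 per arm within a stratum and 194 per arm pooled. Statistical analysis: two-sided levels 0.10 and 0.05. The correlation between the two outcomes is not given and is an assumption here, shown from 0 to 0.9.

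**1. The plan's own figure.** (1.65 + 0.85)² × (1.26² + 1.3²) / 0.5² = 6.25 × 3.2776 / 0.25 = 81.94; the article prints 81. Then 81 × 1.2 = 97.2, taken as 97, and 4 × 97 = 388. The total therefore follows from a 10% level and Fazekas alone.

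**2. Either outcome may succeed, no adjustment.** For two independent tests the chance of at least one false positive is 1 − (1 − α)².
- α = 0.10: 1 − 0.9² = 0.19.
- α = 0.05: 1 − 0.95² = 0.0975.

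Whatever the correlation, the rate cannot exceed 2α, which is 0.20 and 0.10. Bivariate normal calculation with correlation ρ:

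| ρ | p ≤ 0.10 | p ≤ 0.05 |
|---|---|---|
| 0 | 0.190 | 0.0975 |
| 0.3 | 0.185 | 0.095 |
| 0.5 | 0.1755 | 0.091 |
| 0.7 | 0.161 | 0.0835 |
| 0.9 | 0.136 | 0.070 |

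**3. Favourable direction only** (independent outcomes). 1 − 0.95² = 0.0975 at the 10% tier and 1 − 0.975² = 0.049 at the 5% tier, about half the two-sided rates.

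**4. If both had to succeed.** The rate would not exceed the per-test level. The size of the problem therefore depends on a rule the article does not state.

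**5. Fazekas power after 20% dropout.** The pooled SD is √(3.2776 / 2) = 1.280. Power ≈ Φ(0.5 / (1.280 × √(2/n)) − z).
- Within a stratum, n = 97 × 0.8 ≈ 78 per arm: about 0.79 at 10% and 0.68 at 5%.
- Strata pooled, n = 194 × 0.8 ≈ 155 per arm: about 0.96 at 10% and 0.93 at 5%.

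**The case against.** The strongest defence is that this is a Phase II trial that calls itself exploratory and says larger trials must follow. A 10% level is defensible there, and it matches the sizing level. Both tiers are written down in advance, so the natural reading is a 10% working level with a stronger label at 5%. A detailed multiplicity procedure could also sit in a full protocol or analysis plan that is not shown. Much of this stands, and it lowers the severity. It does not remove the point: the article itself fixes two tiers and an unranked pair of primary outcomes, and following its wording gives the rates above.

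A reader might also infer more than the text supports:
- **That the error rate is far above any stated level.** At the 5% tier it is at most 9.75% to 10%, which does not exceed the stated 10%. At the 10% tier it is about double, not more.
- **That the two thresholds add to each other.** Every p ≤ 0.05 is already p ≤ 0.1, so the looser tier alone sets the rate. The harm is that the deciding level is left open.
- **That about one in three is the right figure.** Four independent tests, each outcome in each stratum, would give 1 − 0.9⁴ = 0.344. The total of 4 × 97 does suggest stratum-level sizing, but sizing is not a success rule. The article nowhere says that a result in either stratum counts as success.
- **That the 80% power holds only at the looser level.** This is true within a stratum (68% at 5%) but not for a pooled contrast (93%). The harm cannot be argued from one analysis and the remedy from the other.
- **That the success rule is picked after the result.** Both tiers are prespecified; what is missing is which one decides.

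**Conclusion.** The point holds in a limited form. The article does not say which level or which outcome decides the primary conclusion. Under an either-outcome reading at p ≤ 0.1, the two-sided chance of at least one false difference is up to about 19% (20% at the extreme bound), against 10% in the sizing. It falls as the outcomes become more correlated. The calculation assumes that one success is enough and that no adjustment is made; the article neither states nor excludes either. The contrast between confirming and exploring is a secondary matter of wording, since the overall framing is exploratory. Severity: should-fix.

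**What to change.** 1. In Statistical analysis, name one two-sided level that decides the primary conclusion, and delete the two-tier wording.
2. Test Fazekas first, as the only outcome with a sample-size basis. Test dVRS at the same level only if Fazekas succeeds. This holds the error over the pair at the chosen level and needs no extra subjects.
3. If 10% is kept, it agrees with the Sample size calculation. Label it a Phase II exploratory level, and reword the claim in the Abstract (Conclusion) to match.
4. If 5% is chosen, which is a trade-off and not required by this fix, restate the power for the analysis actually used, with 20% dropout: about 68% within a stratum or about 93% for the pooled stratified contrast.

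**Cost.** dVRS alone can no longer carry a positive conclusion. Under the 5% option, results between 0.05 and 0.10 are no longer called a difference. Table 1 gives recruitment as completed and lists both outcomes as primary, so this is more than a change of wording. It needs a dated amendment made before the codes are opened; if they are already open, the rule must be labelled post hoc.

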## Discussion

CSVD is the most prevalent, chronic and progressive cerebrovascular disease. The disease caused by various factors including arteriosclerosis and inflammation (Chojdak-Łukasiewicz et al., 2021). A previous meta-analysis revealed that HT, hyperlipidemia, diabetes, and smoking are the risk factors for CSVD (Wang et al., 2021). Moreover, the effects of these risk factors are accelerated by aging (Wang et al., 2021). Therefore, this calls for the development of measures for the early management of these factors, particularly HT. The international STRIVE (Wardlaw et al., 2013) and the Chinese consensus on the diagnosis and therapy of CSVD (Huang, 2015; Hu et al., 2021) released a diagnosis and treatment guidelines for its clinical management. Since then, research on the pathogenesis and treatment of HT-CSVD has gradually attracted attention. The currently used symptomatic and supportive treatment schemes of HT-CSVD involve the management of blood pressure variation (Chen et al., 2019; Zhang et al., 2019), thrombolysis (Powers et al., 2019), antiplatelet therapy (Kim et al., 2020), lipid reduction (Xiong et al., 2014) and others. The above schemes help prevent bleeding and coagulation, as well as suppress stroke and cognitive impairment. Nevertheless, the efficacy of thrombolysis, antiplatelet, and statin drugs is debatable due to the lack of adequate clinical research evidence and the risk of bleeding (Cannistraro et al., 2019). Furthermore, the clinical management of HT-CSVD patients faces many problems and challenges owing to its complex pathogenesis, pathology, and clinical manifestations (Liu et al., 2018). In this regard, identifying effective multi-target Chinese medicines remains a critical research direction of HT-CSVD.

Based on TCM theories and clinical evidence, our research team developed NTF as a new Chinese medicine formula for treating cerebral vascular diseases. We performed a series of investigations to evaluate the pharmacology, efficacy, and safety of NTF for more than 20 years. Studies indicate that NTF and its extracts minimize the cerebral infarct size and improve neurological function by inhibiting inflammation, oxidative stress, and apoptosis (Liao et al., 2015; Lan et al., 2020; Yang et al., 2021; Zhao et al., 2021). Considering the shared pathogenesis pathways between HT-CSVD and ischemic stroke, and if HT-CSVD is not treated in time, it can gradually progress to stroke. Therefore, we speculate that NTF capsules may also be effective against HT-CSVD. Recruitment of participants commenced in July 2020, and the trial is expected to be completed in December 2022. The findings from this study will reassess the effecacy and safety of NTF capsules through a multi-center, double-blind RCT. Moreover, the results of this study will guide the clinical treatment of HT-CSVD and the prevention of other conditions, including stroke and other cerebral macrovascular diseases.

Noteworthy, this trial is still an exploratory study, hence the sample size and clinical research sub-centers may be insufficient. Also, improving participant compliance with medication is a critical issue and worthy of attention, considering that they are elderly with basic diseases. Of importance is that the intervention period of this study is relatively short, and the long-term efficacy and safety will be determined in follow-up studies. Therefore, additional multicenter-clinical trials with large sample sizes and long intervention periods are essential for comprehensive research.

## Conclusion

In summary, this protocol will provide in-depth study information according to the SPIRIT-TCM extension statement. By strictly implementing the trial protocol, this study will generate high-quality evidence on the effecacy and safety of NTF capsules in treating HT-CSVD with QDBS syndrome. Moreover, the results may also help identify the potential mechanism of NTF capsules in treating HT-CSVD with QDBS syndrome. Nonetheless, more clinical trials with large sample sizes and long intervention periods will be required in the future to validate the findings of this trial.
